###### Community dialogues: delivery and facilitator support and monitoring

The facilitators will be trained to provide brief, evidence-based information in a lecture-style format about one or more focal health issue(s) to community members at the start of each CD, supported by their training, a facilitator guide and an accompanying pictorial flipbook (to visually illustrate the health issue(s) to participants). However, they will also be given the flexibility to tailor each CD to the specific needs and requirements of the community. As per their training, they will then facilitate discussions among community members about the health issue(s) covered and how they might address them within their community. The final goal is for each CD to conclude with the participants committing to one or more courses of action for them and their communities to undertake to help address the focal health issue(s) covered within their community, based on the collective discussions. The CDs are intended to be highly participatory and inclusive, with facilitators trained to encourage all participants to share their experiences, voice their concerns and contribute to decision making. Facilitators are also trained to encourage participants to spread information through word of mouth, set a positive example among family, friends and neighbors, and to hold each other to account for applying decisions reached during CDs.

Each facilitator will also be supervised by either the community healthcare provider from the CC covering the community in which they will deliver and facilitate the CDs, or by the Assistant Health Inspector (the supervisor of the community healthcare provider) of their subdistrict, or by a Health Assistant (basic healthcare provider and responsible for the Expanded Immunization Program at a local level) from their subdistrict. Facilitators will meet with their supervisor prior to their first CD to help plan, and then after every subsequent CD to discuss how the CD went, including any feedback from participants (which the facilitators will be trained to collect via a form), and to plan for the next CD.

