Therefore, we concluded that for our primary outcomes we would look at measures of correct and appropriate knowledge in relation to antibiotics and ABR in relation to human and animal health and the environment, as the CDs were explicitly designed to address and improve such knowledge. However, as no relevant measures of correct and appropriate knowledge exist for the topics and issues our unique set of CDs address, we had to create two bespoke primary outcomes measuring knowledge levels (see below). The questions used to create them were developed by members of the entire research team having specific subject matter expertise, with backgrounds in clinical practice, veterinary practice, public health, environmental-human health and water, sanitation and hygiene. The process of developing these outcomes involved first conducting two literature reviews.

First, we looked for any journal article conducting a survey in any LMIC on community members’ knowledge, attitudes and practices related to antibiotics within the last 10 years. Second, we collated the key messages for members of the public and farmers from recent guidance related to antibiotics, published by international and national organizations including the World Health Organization, World Organization for Animal Health (38), the European Union (39). We then looked at the content of the CDs and, alongside the findings of the two literature reviews, developed a set of questions that tested understanding of all the key messages we would want the full CD program to pass onto those attending CDs or hearing about them from family and friends. This set of questions was also refined by taking into consideration the local context in which the CDs would be run.

There then followed several rounds of iterative feedback and modification within the team. Lastly, we then pilot tested the draft questions with one female and one male from a similar rural community outside the study area. This pilot testing looked at how understandable the questions were and how acceptable and feasible the questionnaire was to the two participants. It also looked at the correctness of the skip patterns in the questionnaire. Based on the findings of the pilot testing we then amended and updated the questionnaire accordingly.

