### Data collection, management and monitoring

#### Questionnaire

During the baseline and endline surveys we will collect all data via a digital questionnaire. A Microsoft Word version of the questionnaire is available in the Supplementary materials (see *Survey questionnaire* in Supplementary file 2). The questionnaire will record basic trial related data, such as the date and time, cluster and village identifier codes, and participant consent. It will also record a range of data on participants’ socio-demographic characteristics, such as their age, sex, education levels and animal ownership details. It will also record participants’ responses to the questions that will be used to generate the primary and secondary outcomes. Our endline survey questionnaire will also contain a series of questions about attendance and/or awareness of the CDs (both among participants and their family/friends etc.) to allow some of our planned subgroup analyses. The questionnaire was developed into an Android-based app using the commercial Survey CTO platform^3^, which in turn is based on the Open Data Kit^4^ platform. In the field the questionnaire will be completed by the data collectors via tablets running the Android operating system.

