##### Effect of engagement with the community dialogue approach intervention

As we do not expect all adult community members to engage with the CDA intervention we will also estimate the individual-level causal effect on the two primary outcomes of (1) having attended one or more CDs (yes/no) and (2) the number of CDs attended (i.e., the linear relationship between the number of CDs attended and the expected mean of the primary outcome). As these treatment effects are non-randomly assigned we will use an instrumental variable approach to try and account for likely confounding, which will estimate these two causal effects among the population of individuals who would be predicted to always comply with the intervention if it was available (i.e., attend the CDs if they were available in their communities) (50). These types of treatment effects are therefore often referred to as complier average causal effects or local average treatment effects (50). Specifically, we will use the two-stage residual inclusion instrumental variable approach with cluster treatment allocation as the instrument, as opposed to the more common two-stage least squares approach, which is more suitable for modeling binary treatments and non-continuous outcomes (51).

To estimate the causal effect on both primary outcomes of attending one or more CDs the two-stage residual inclusion process will involve first fitting a generalized linear model with Bernoulli errors and a logit link to an outcome indicator of whether a survey participant reports having attended one or more CDs, with covariates for cluster treatment allocation, subdistrict, sex (female/male), age (years) and age^2^, education level (none, less than primary, primary, less than secondary, secondary or less than higher secondary, higher secondary, graduate/post-graduate), employment status and main role in the last 30 days (no paid/in-kind work, nonprofessional/manual, personal business, professional), ownership of any animals by the household for food/economic purposes (yes/no), number of individuals living in the household, and the cluster-level baseline mean of the relevant primary outcome. We will then use the model to compute every participants’ model-predicted outcome value based on their observed covariate values, and then subtract those predicted outcomes from a numeric indicator of whether the participant attended one or more CDs (coded as 1) or not (coded as 0) to create residuals for each participant.

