For an instrumental variable analysis to produce an unbiased estimate of the treatment effect of interest there are four key assumptions that must be met (54). Although there are many other possible sources of bias, and meeting these assumptions does not guarantee an unbiased estimate, we believe the analysis will not at least not violate these assumptions in any substantial way. (1) The instrument must be conditionally randomized with respect to the outcomes of interest and the treatments of interest. As we will be using the random allocation of clusters to the assigned treatment group as the instrument this assumption will be satisfied. (2) The instrument must effect the treatments of interest. Unless there are no survey participants in the intervention group communities who engage with the intervention this assumption will be satisfied. (3) The instrument must have no direct effect on the outcomes of interest and only affect them indirectly via the treatments of interest (commonly known as the exclusion restriction). As we are using the random allocation of clusters to treatment groups as the instrument this random allocation itself clearly has no causal effect on the outcomes of interest (only the treatment implemented, which may or may not be received by a participant), and so this assumption will be satisfied. (4) There are no survey participants who would attend CDs if they were available in their communities and if they were not encouraged to attend, but who would, conversely, not attend any CDs if they were available in their communities and if they were encouraged to attend (the community volunteers running the CDs will be encouraged to encourage members of their community to attend CDs). This is more speculative but, given the unusual behavior required, if such individuals do exist we believe they will be very infrequent.

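### The protocol declares the exclusion restriction met because allocation is random, but the intervention is designed to reach non-attenders by word of mouth; if it does, the attendance effect is expected to be overstated

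*Protocol article*

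**What the plan says.** All references are to the protocol article.

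- **Exposure and estimator.** The section on the effect of engagement with the intervention gives the reason for the analysis: "we do not expect all adult community members to engage with the CDA intervention". It defines two exposures, both the participant's own: attendance at one or more CDs (yes/no) and "the number of CDs attended". The estimator is the "two-stage residual inclusion instrumental variable approach with cluster treatment allocation as the instrument".
- **The assumption.** The same section defines exclusion correctly: the instrument may influence outcomes only by way of the treatments of interest. It then declares exclusion satisfied on the ground that "this random allocation itself clearly has no causal effect on the outcomes of interest", and says it believes none of the four IV assumptions is materially violated.
- **The intervention.** Under delivery and facilitator support, facilitators are trained to "encourage participants to spread information through word of mouth" and to have attenders set an example to those around them.
- **The outcome.** Under outcome rationale and development, the knowledge questions test the key messages that the programme should convey to "those attending CDs or hearing about them from family and friends".
- **The data.** Under Questionnaire, the endline survey carries "questions about attendance and/or awareness of the CDs", covering participants and their family and friends.

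**The concern.** The reason given for exclusion is a reason for a different assumption. Random allocation makes the instrument independent of participants' characteristics, which is the first of the four listed assumptions. It does not settle by which route allocation changes knowledge.

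Here a second route is part of the design. A villager who attends nothing but learns from a neighbour who did attend has gained knowledge because of allocation, without any change in the exposure variable. An IV analysis that imposes exclusion credits that gain to the attenders.

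The estimates answer how much attending a dialogue changes knowledge. If part of the gain comes from diffusion, they would answer it wrongly without any sign of it. The bootstrap intervals do not reflect this bias, and the planned Gaussian sensitivity model shares it.

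**Working it through.** The protocol states no expected attendance, attendance effect or spillover, so there is no figure of its own to reproduce. The check is of direction, with size under assumed inputs.

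**Step 1: the ratio (Wald) identity.** Let p be the share attending in intervention clusters (attendance in control clusters taken as 0), d the true attendance effect, and s·d the gain among intervention-arm non-attenders.

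- Difference between arms: p·d + (1−p)·s·d
- Ratio estimate: difference ÷ p = d·[1 + (1−p)s/p]

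This equals d only if s=0 or p=1, and the protocol does not expect p=1. Inflation factors:

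| p (assumed) | s=0.2 | s=0.5 |
|---|---|---|
| 0.2 | 1+0.8×0.2/0.2 = 1.80 | 1+0.8×0.5/0.2 = 3.00 |
| 0.3 | 1+0.7×0.2/0.3 = 1.47 | 1+0.7×0.5/0.3 = 2.17 |
| 0.5 | 1+0.5×0.2/0.5 = 1.20 | 1+0.5×0.5/0.5 = 1.50 |

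**Step 2: the planned estimator.** Two-stage residual inclusion (2SRI) is not the ratio estimator, so it was simulated: 50 clusters of 44, 25 items, logit first stage, an unmeasured confounder, 1% attendance in control clusters, true effect 10 points, 60 repetitions per setting. Mean estimates at p=0.3, with allocation left out of the second stage:

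| s | Ratio formula | Gaussian second stage | Poisson second stage |
|---|---|---|---|
| 0 | 10.0 | 10.7 | 8.7 |
| 0.1 | 12.3 | 11.3 | 9.5 |
| 0.25 | 15.8 | 13.9 | 12.6 |
| 0.5 | 21.7 | 18.6 | 18.5 |

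The estimates rise with spillover, but less far than the ratio formula: at s=0.5 about 1.85 times the truth (18.5/10 and 18.6/10) against 2.17. At p=0.2 and s=0.5 they were 23.2 (Gaussian) and 24.0 (Poisson) against 30.0. At p=0.5 and s=0.5 they were 13.9 and 13.5 against 15.0.

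**Step 3: the second stage as written.** The protocol lists allocation among the first-stage covariates and then carries the remaining first-stage covariates into the second stage. Read literally, allocation is retained there. Exclusion is then not imposed, and identification rests on functional form. In the same simulation at p=0.3, moving s from 0 to 0.5 changed the estimate from 9.3 to 4.5 (Gaussian) and from 5.1 to −0.9 (Poisson). The direction reverses.

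No factor was computed for the number of dialogues attended. The same bypass exists there, but its size is not given by the formula above.

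**The case against.** The best defence is the protocol's own qualification that allocation acts only through the treatment implemented, which a participant may or may not receive. This does not rescue the claim. The treatment implemented in a village is not the analysed exposure, which is the participant's own attendance, and what is implemented is meant to travel further than the meeting. The section also concedes that other sources of bias may exist, but it still calls this assumption satisfied.

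Other objections do stand, and they limit the point:

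- **Certainty of direction.** A reader might infer that the attendance effect will be overstated whatever happens. The documents do not support that. Inflation needs positive spillover, which is intended but not established, and a second stage without allocation. Under the literal reading of the second stage, the simulated estimates fell.
- **An upper bound.** A reader might want to report the estimates as upper bounds. With little spillover the simulated Poisson model sat below the truth (8.7 and 9.5 against 10), so that label would be a new unsupported claim.
- **Size.** The table of factors describes a ratio estimator for yes/no attendance at assumed p and s. It is neither the bias of the planned model nor that of the per-dialogue effect.
- **What the questions capture.** The mention of family and friends describes the audience for the key messages. It shows that indirect learning was foreseen, not that the items were written to detect it.
- **Reach.** This is a supplementary analysis. The cluster-level analyses by allocation properly include spillover within clusters.

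**Conclusion.** The statement that exclusion will be satisfied is wrong as written. Its justification supports independence, and the protocol's own account of the intervention describes a planned route from allocation to knowledge that bypasses own attendance. Confidence in this is high.

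Confidence in direction is moderate. If word of mouth works as intended and the second stage follows standard 2SRI practice by omitting the instrument, overstatement is expected, and it grows as attendance falls.

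The size cannot be derived from the document. Over assumed p from 0.2 to 0.5 and s from 0.2 to 0.5, the ratio formula runs from 1.2 to 3.0 times the true effect. The simulated planned model showed less inflation than the formula at s=0.5. The conclusions that the attendance estimates can support change; the primary treatment effects do not. The change should be made, but the trial's main result does not depend on it.

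**What to change.** 1. Withdraw the statement that exclusion is satisfied and, for this assumption, the claim of no material violation.
2. Name the word-of-mouth route. Say that, if it raises knowledge among non-attenders, the attendance effect is expected to be overstated. Do not call the estimate an upper bound.
3. State explicitly that cluster allocation is left out of the second-stage models.
4. Add a sensitivity analysis of the attendance effects over a range of assumed non-attender gains, for example s = 0 to 0.5. Endline attendance in the intervention clusters supplies p, so only s has to be assumed.
5. Optionally, repeat the IV analysis with exposure defined as attended or heard about the CDs, using the endline items already planned. This is supplementary and has a different estimand: it mixes very different doses and does not recover the effect of attending.

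The cost is wording in the statistical analysis plan, some additional model runs for two outcomes with their bootstraps, and a less firm causal statement. No new data are needed.

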#### Secondary outcomes

##### General considerations

We will not adjust any of these results for multiple testing and treat them as exploratory. We do not plan to compute effect modification results for any secondary outcomes but we may do so as a strictly exploratory process for any secondary outcomes if we find clear evidence of a treatment effect.

##### Whole sample secondary outcomes

Both of our secondary outcomes that apply to the whole sample (1. antibiotic awareness and 2. the presence of appropriate handwashing facilities in the household) are binary. For these secondary outcomes we will also estimate covariate-adjusted and covariate-unadjusted cluster-average treatment effects using similar two-stage cluster-level analysis methods as described above (see *Main analyses*) but adapted for binary outcomes to produce treatment effect measures on the risk difference scale (44, 49). For both sets of results the only difference in the approach is that in the first stage we will use a generalized linear model with Bernoulli errors and a logit link to compute the cluster-level model-predicted outcome values by taking the mean of the individual-level model-predicted outcome probabilities within each cluster, but the rest of the method remains the same.

These risk difference scale treatment effects will be our primary focus but, as recommended by the *Consort 2010 statement: extension to cluster randomized trials* (47), we will also compute both covariate-adjusted and covariate-unadjusted cluster-average treatment effects for these binary outcomes on the ratio-scale (as supporting auxiliary results). We will again use the same broad two-stage approach for both sets of results but slightly further modified.

Specifically, in the first stage we will again use a generalized linear model with Bernoulli errors and a logit link to compute the cluster-level model-predicted outcome values, but instead of creating cluster-level difference residuals we will create cluster-level ratio residuals by dividing the cluster-level observed mean outcome values by the cluster-level model-predicted outcome values. Then in the second stage we will again use an ordinary least-squares linear regression but with the natural logarithm of the cluster-level ratio residuals as the outcome and a covariate for treatment group. Lastly, by transforming the regression coefficient for the treatment group covariate along with its t-based 95% confidence intervals via the exponential function we then obtain an estimate of the treatment effect on the risk ratio scale (technically as a ratio of the geometric mean of the outcome in each treatment group) (44, 49).

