### Secondary outcomes valid for the entire sample

The following secondary outcomes are valid for the entire sample.

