#### Antibiotic/antimicrobial resistance awareness

A binary indicator of self-reported awareness of the existence of antibiotic/AMR. Specifically, whether a participant responds “yes,” as opposed to “no/do not know,” to the question “Have you heard of any of the terms ‘antibiotic resistance’, ‘antimicrobial resistance’ or ‘drug resistance’?” This outcome is to allow us to explore whether the CDs may improve simple reported awareness of the existence of ABR/AMR, given an awareness of ABR is the most basic and fundamental starting point required to begin to understand the problems associated with antibiotic misuse.

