### Secondary outcomes valid for subgroups of the sample

The following outcomes are only valid for a subgroup of the sample, or are restricted to only being collected from a subgroup of the sample, as described in each case.

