##### Subgroup-specific secondary outcomes

Our remaining secondary outcomes are only valid for subgroups of the sample, such as those individuals who report being aware of what an antibiotic is. For all these outcomes the sample can be divided into individuals within the subgroup where the outcome is valid and individuals not in that subgroup. As these subgroups may be at least partly determined post-randomization by the intervention (e.g., the intervention may well affect whether an individual in the intervention group is aware of what an antibiotic is) a standard analysis of the treatment effect, by simply subsetting the data, would be prone to post-randomization selection bias (55). For these secondary outcomes we will therefore use a slightly-modified, regression-based approach that aims to adjust for this potential selection bias when estimating cluster-level treatment effects. In the literature these are known as survivor average causal effects, as these types of methods were originally developed to address selection bias in the context of survival/death creating subgroups of individuals where the outcome is valid or not (e.g., you cannot measure health outcomes if the patient has died) (56).

Our approach aims to estimate the cluster-average causal effect of treatment among the subgroup of individuals who would be part of that subgroup irrespective of any effect of the intervention (e.g., among individuals who would be aware of what antibiotics are irrespective of any effect of the intervention on their awareness of what antibiotics are). As with our whole-sample secondary outcomes, we will compute these treatment effects on both the absolute difference and ratio scales as the difference/ratio in the cluster-level percentage occurrence of the relevant outcome event between treatment groups, among the subgroup of individuals for whom the outcome is valid.

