See (56) for full details of the original method. In summary though, we will first fit a generalized linear model with Bernoulli errors and a logit link to the binary indicator of whether an individual is in the subgroup where the ultimate outcome of interest is valid not (e.g., whether they report being aware of what an antibiotic is or not, with the ultimate outcome of interest being whether they report being aware of what ABR is). The model will contain covariates for cluster treatment allocation, subdistrict, sex (female/male), age (years) and age^2^, education level (none, less than primary, primary, less than secondary, secondary or less than higher secondary, higher secondary, graduate/post-graduate), employment status and main role in the last 30 days (no paid/in-kind work, nonprofessional/manual, personal business, professional), ownership of any animals by the household for food/economic purposes (yes/no), number of individuals living in the household, and the cluster-level baseline mean of the relevant secondary outcome. We will then use the model to compute outcome probabilities for every participant and subtract these from 1 to create an adjustment factor that will be used in the next stage to adjust for any selection bias due to the subgroup being determined post-randomization.

We will then subset the data to only include those participants who are in the subgroup for which the ultimate outcome is valid, and then fit a generalized linear model with Bernoulli errors and a logit link to the relevant ultimate secondary outcome of interest (e.g., reported awareness of what ABR is). This model will include covariates for the selection bias adjustment factor and all the covariates included in the first stage model. Unlike in (56) this model will also be weighted by the inverse of the cluster sample sizes to produce cluster-average causal effect estimates (40). Then, as described above (*Effect of engagement with the community dialogue approach intervention*), we will use marginal effects methods to compute survivor average causal effect estimates on the difference and ratio scales. Lastly, we will compute 95% confidence intervals for all these treatment effect estimates based on the same clustered bootstrap approach described above (*Effect of engagement with the community dialogue approach intervention*).

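### Awareness of antibiotic resistance is defined as a whole-sample secondary outcome but assigned to the subgroup-only analysis, which changes its population, estimand and method

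*Protocol article*

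**What the plan says.** **Definitions.** The section on secondary outcomes for the entire sample opens: "The following secondary outcomes are valid for the entire sample". Three outcomes follow: antibiotic awareness, ABR/AMR awareness and handwashing facilities. The second is defined as "A binary indicator of self-reported awareness of the existence of antibiotic/AMR". It is scored yes against no or do not know, and the definition does not require the respondent to know of antibiotics. Restricted outcomes begin only in the next section, which opens: "The following outcomes are only valid for a subgroup of the sample".

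**Aims.** The Methods part of the Abstract and the Objectives section both name awareness of ABR, with no restriction to people who know of antibiotics.

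**Analysis.** The section Whole sample secondary outcomes counts two: "Both of our secondary outcomes that apply to the whole sample (1. antibiotic awareness and 2. the presence of appropriate handwashing facilities". The section Subgroup-specific secondary outcomes continues: "Our remaining secondary outcomes are only valid for subgroups of the sample". It then takes antibiotic awareness as the subgroup indicator, "with the ultimate outcome of interest being whether they report being aware of what ABR is", and uses the same example again for the second-stage model. Before that model is fitted, "We will then subset the data to only include those participants who are in the subgroup for which the ultimate outcome is valid". The effect sought is the one "among individuals who would be aware of what antibiotics are irrespective of any effect of the intervention".

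**The concern.** One named outcome has two incompatible specifications. Under the definitions, it is compared between arms in everyone surveyed, by the two-stage cluster-level method. Under the analysis section, it is modelled only in people who know of antibiotics. The target there is a survivor-average effect, and the intervals come from a clustered bootstrap.

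The second route answers a narrower question. By construction it leaves out people who learn of antibiotics because of the intervention, and they are among those in whom a gain in ABR awareness could be expected. It also replaces a comparison protected by randomisation with one that depends on a model for subgroup membership.

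This is not detail that a statistical analysis plan would normally supply. The article has already fixed two answers, and an analyst cannot follow both.

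**Working it through.** **1. Count the outcomes in each section.**

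| | Whole sample | Subgroup only | Total |
|---|---|---|---|
| Outcome definitions | 3 (antibiotic awareness, ABR awareness, handwashing) | 5 (sharing, personal use, use in children, water sources, animal feed) | 8 |
| Analysis section | 2 (antibiotic awareness, handwashing) | the remaining 6 | 8 |

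The totals agree, and the one outcome that moves is ABR awareness. Both mentions in the worked example confirm the move, so it is more than a slip in one word.

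**2. Which reading fits the rest of the text?** Where the article wants a restriction to antibiotic-aware people it says so, for sharing, personal use, use in children and animal feed. It does not for ABR awareness. The survivor-average method is justified by analogy with death, where the outcome does not exist outside the subgroup. Awareness of resistance exists for everyone: a person who has not heard of it counts as not aware.

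**3. Numbers in the outcome model.** Reproducing the planned sample: 2 villages × 22 = 44 per cluster; 44 × 25 = 1,100 per arm; 44 × 50 = 2,200 per survey.

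The definition of antibiotic awareness cites a 2018 survey in this setting with about half of adults aware. The number in the second-stage model is 2,200 × share aware:

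- 40%: 880 kept, 1,320 left out
- 50%: 1,100 kept, 1,100 left out
- 60%: 1,320 kept, 880 left out
- 70%: 1,540 kept, 660 left out
- 80%: 1,760 kept, 440 left out

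Only the 50% row rests on a figure in the article; the others are an assumed range.

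**4. Precision lost by subsetting.** Effective number per arm = 25m / (1 + (m − 1) × ICC), with m = 44 for everyone and m = 22 for half.

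- Assumed ICC 0.1: 1,100 / 5.3 = 208 against 550 / 3.1 = 177
- Assumed ICC 0.3: 1,100 / 13.9 = 79 against 550 / 7.3 = 75

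Because clustering dominates, the loss is modest.

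**5. Difference in estimand.** For illustration, count people unaware of antibiotics as not ABR-aware. Then the whole-sample rate is P(antibiotic-aware) × P(ABR-aware given antibiotic-aware). All rates are assumed.

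- Antibiotic awareness 50% to 70%, ABR awareness among the aware 40% in both arms: 0.70 × 0.40 − 0.50 × 0.40 = 0.28 − 0.20 = **+8 points** in the whole sample. Among the always-aware the effect is **0**, if their rate is also unchanged. The whole gain comes from the newly aware: 0.20 × 0.40 = 0.08.
- Antibiotic awareness 50% in both arms, ABR awareness among the aware 40% to 50%: 0.50 × 0.50 − 0.50 × 0.40 = **+5 points** in the whole sample, **+10** in the subgroup.

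The two analyses can differ in either direction, and one can show an effect where the other shows none.

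**The case against.** **The outcome is exploratory.** It is one of eight secondary outcomes, all unadjusted for multiplicity and treated as exploratory. The primary outcomes, randomisation and sample size are unaffected. This stands and limits the severity.

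**The questionnaire is not visible.** It sits in a supplement and has automated skips. If the ABR item was put only to antibiotic-aware people, one could argue that the definitions are the text to correct. The possibility is real, and it means that the coding rule must depend on the skip pattern. It does not overturn the whole-sample classification, which both the section heading and the unrestricted aims support.

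**Stronger readings that the documents do not support:**

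- A reader might infer that half the sample is discarded. The share is a 2018 figure; awareness at endline may be higher and may differ by arm. The first-stage membership model still uses every participant.
- A reader might infer that every antibiotic-unaware respondent should be scored as not aware of resistance. The question also offers the term drug resistance, so someone unfamiliar with antibiotics could truthfully say yes. If the item was asked of everyone, such a recode would overwrite real answers.
- A reader might take the outcome's own paragraph to state a community-wide purpose. It does not. The whole-sample status comes from the section heading and the stated aims.

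**Conclusion.** The article is wrong as written: it puts ABR awareness in one class in the outcome definitions and in the opposite class in the analysis, and nothing elsewhere in the text resolves this. Followed literally, the analysis section would report an effect among people who would know of antibiotics regardless of the intervention, in place of the effect in all adults surveyed.

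The change of estimand is the main consequence. Under the assumed rates above, the results are +8 points against 0, or +5 against +10. These show what can happen and are not forecasts. The reduction to about 1,100 of 2,200 in the second-stage model holds only if antibiotic awareness stays near the 2018 level, and its cost in precision is small beside the change of question.

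This should be fixed. It does not threaten the trial's main conclusions, because the outcome is secondary and exploratory.

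**What to change.** - In Whole sample secondary outcomes, replace the count of two by three and add ABR/AMR awareness, analysed by the two-stage cluster-level method on all participants.
- In Subgroup-specific secondary outcomes, replace the ABR awareness example in both places with a true subgroup outcome, such as sharing of antibiotics.
- State how the item was administered. If it was asked of everyone, use the recorded answers. Only if the questionnaire skipped it for antibiotic-unaware respondents, code them as not aware and say so. Apply the same rule at baseline and endline.
- Carry the same classification into the statistical analysis plan, and settle it before results are seen by arm.

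The cost is a wording change to the protocol and analysis plan. No new data are needed.
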